### Portion size

Portion size was assessed using portion size photographs from the Dietary Questionnaire for Epidemiological Studies Version 2 (DQES v2), FFQ from the Cancer Council Victoria [39]. These photos are used to calculate a single portion size factor (PSF) to indicate whether on average a person eats median size serves (PSF = 1), more than the median (PSF >1), or less than the median (PSF <1) serve sizes for main meals. The DQES was developed specifically for use in Australian adults by the Cancer Council of Victoria as an update of a FFQ used in a cohort of Australian volunteers aged 40-69 years. Both the development of the questionnaire [40] and its validation have been reported previously [41].

### Alcohol Consumption

Alcohol consumption was measured using an adaptation of the Australian Government Department of Veteran Affairs, Alcohol Use Disorders Identification Test (AUDIT) 2009 [42]. This instrument has been shown to be a valid and reliable measurement tool in determining alcohol use disorders and alcohol misuse [43,44].

### Physical activity and nutrition cognitions

Physical activity and nutrition beliefs were assessed using a number of validated instruments: physical activity self efficacy [45], physical activity outcome expectation [46], physical activity social support [47], physical activity intention [48], nutrition self efficacy [49], nutrition outcome expectations [50], nutrition social support [47] and nutrition intention [48].

### Sedentary Behaviours

Sedentary behaviours were assessed using an adaptation of the Sitting Questionnaire, which has been shown to be both a valid and reliable measure of sitting time in various domains [51,52].

### Quality of Life

Quality of Life and general health was assessed using the UK short form 12 (SF-12) questionnaire [53,54].

### Sleepiness

Daytime Sleepiness was assessed using the Epworth sleepiness scale which is a valid measure of general daytime sleepiness [55].

### Sexual Function

Sexual Function was assessed using the International Index of Erectile Function-5 (IIEF-5) questionnaire which has been shown to be a valid measure of erectile function [56].

### Process measures

Adherence to self-monitoring (total number of daily diet entries, daily exercise entries and weekly weigh-ins) will be calculated from diaries for both treatment arms. In addition to this, men will hand in their SHED-IT support booklet at the 3- and 6-month time points, to be photocopied and posted back. We will also administer a detailed process questionnaire to examine men's perceptions of the SHED-IT program. This will include scales, individual items and open-ended questions that require men to describe the strengths and weaknesses of the program along with their suggestions for improvement. The process evaluation will cover issues such as the study feasibility, opinion of the allocated study group, use and appraisal of components of each intervention and their levels of overall satisfaction. We will also ask how much participants would be willing to pay for the offered intervention. The process evaluation will be administered at the 6-month time point.

### Sample size

The sample size calculation is based on the primary outcome of weight loss at 6 months, which we have assumed will have a standard deviation of 5 kg [24,57]. Thirty six men in each treatment group will give the study 80% power to detect a difference in weight loss between groups of 4 kg at the 1.5% significance level using a two sided test. We have used an alpha of 0.015 to control the Type I error rate for multiple comparisons. A sample size of 150 men was required to allow for an attrition rate of 28%.

### Randomisation

Participants were randomised at an individual level by the trial statistician who will not have any contact with participants during the trial. Allocation was stratified by BMI category calculated at the baseline assessment (overweight, obese I, obese II) and the allocation sequence within strata was generated by a computer-based random number-producing algorithm in block lengths of six. Randomisation codes are stored in a restricted computer folder, which is not accessible by those assessing participants, those involved in group allocating participants or those participating in data entry for the study. Complete separation was achieved between the statistician who generated the randomisation sequence and those who concealed allocation from those involved in implementation of assignments.

### Allocation

Study information for the three different groups was pre-packed into identical black plastic opaque envelopes and consecutively numbered within the three BMI categories and ordered according to the randomisation schedule. The packing and sequencing of these envelopes was completed by a research assistant who was not involved in enrolment, assessment or allocation of participants. Study participants completed all baseline assessments before proceeding to a separate room to meet with a research assistant who was not involved with the baseline assessments. The allocation sequence was concealed during this process. Participants' BMI category was calculated from the baseline measurements and the participant was allocated the next available number in that BMI category before being provided with their information pack. At this point the envelope was opened by the research assistant and details of the particular information pack were provided to the participant using a standardised protocol.

### Data management, quality assurance and exclusion of bias

Randomisation was undertaken by the trial statistician and measures will be taken by trained staff at all times points. In order to ensure accurate and consistent measurements, the study weight scale was professionally calibrated and the height scale checked and recalibrated daily before measurements commenced. All assessments were completed by staff blinded to treatment allocation. When men are contacted (via phone and email) to book in for follow-up assessments they will be asked not to inform data collection personnel of their group allocation. Data will be entered by research assistants blind to group allocation and a program of plausibility checks will be used to identify unrealistic values. The primary outcome measure (weight) will be double entered to ensure accuracy and a random 20% sample of all other measures will also be double entered.

### Statistical methods

Analyses will be performed using Stata Version 11 or later. All variables will be checked for plausibility and missing values. Data will be presented as mean (sd) for continuous variables and counts (percentages) for categorical variables. Differences between groups at randomisation and characteristics of completers versus dropouts will be tested using independent *t *tests for continuous variables and chi-squared (χ^2^) tests for categorical variables. The significance level for the comparison of baseline characteristics will be set at 0.05.

A series of Generalised Linear Mixed Models (GLMMs) with a random intercept for individual will be used to test for differences between treatment groups in the mean level of weight after treatment. Separate models will be fit for each of the pair-wise comparisons (*Resources *vs. *Control*; *Online *vs. *Control*; and *Resources *vs. *Online*). The independent variables in the model will include a variable for treatment group, time (treated as categorical with levels baseline, 3-months and 6-months) and the group-by-time interaction. The model will also include a term for the stratifying variable of BMI group at baseline. The coefficient and p-value for the group-by-6 month interaction term will be used to determine the efficacy of the interventions. Similar models will be used to examine differences in change in other outcome measures.

Using the same approach, additional exploratory models will be used to examine subgroups of the study population. These models will contain the variable that identifies the subgroup (such as SES) and of interest will be the 3 way interaction of treatment group by time by SES. We will also examine a range of secondary outcomes to support the primary outcome (e.g. reduction in waist circumference, increase in physical activity, reduction in kilojoule intake). Additional exploratory models will be fitted to examine if the men who have the greatest reduction in weight are also those who have the greatest improvements in the secondary outcomes.

Statistical significance of the primary efficacy analysis (3 pair-wise comparisons) will be based on Hochberg's multiple testing procedure with the family wise error rate held at 5%. All secondary hypothesis tests will be performed using a 2-sided 5% significance level. In addition, linear regression and GLMMs will be used to describe relationships among the various dependent and independent variables.

A per protocol analysis will also be conducted and include men who complied with treatment from the *Online *and *Resources *component. Men who complied well with the assigned treatment, defined as completion of requested daily eating and exercise diaries (n >40) over the 3-month period and weekly check-ins (n >10). Results of the per-protocol group will be compared with non-compliers in each group i.e. those who did not meet the above adherence recommendations.

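### The random-intercept-only model holds the stated 5% family-wise error rate only if the two 3-month weight changes are, on average, at least as variable as the 6-month change

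*Protocol article*

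**What the plan says.** The Statistical methods section of the protocol article names one within-person structure for the primary outcome: "A series of Generalised Linear Mixed Models (GLMMs) with a random intercept for individual will be used to test for differences between treatment groups". The fixed effects are treatment group, "time (treated as categorical with levels baseline, 3-months and 6-months) and the group-by-time interaction", plus a term for baseline BMI stratum. "Separate models will be fit for each of the pair-wise comparisons", which gives three two-arm models. The decision rule is explicit: "The coefficient and p-value for the group-by-6 month interaction term will be used to determine the efficacy of the interventions". Significance of the three comparisons "will be based on Hochberg's multiple testing procedure with the family wise error rate held at 5" per cent. No other residual covariance, random slope or robust standard error is named. Similar models are planned for the other outcomes.

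The Sample size section gives the only variability figure, for weight loss at 6 months, "which we have assumed will have a standard deviation of 5 kg". No SD is given for 0-3 or 3-6 month change, and no correlation between visits.

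**The concern.** A random intercept with independent, constant-variance residuals gives every visit the same variance and every pair of visits the same correlation. Under that model, weight change has the same variance over 0-3, 3-6 and 0-6 months. The decisive contrast spans the longest interval, but its standard error comes from one residual variance pooled over all three. If men's weights drift apart over time, the 6-month change is more variable than the pooled figure and its standard error is understated.

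The confirmatory conclusions are at stake. Hochberg's procedure controls the family-wise rate only if the p-values fed into it are valid. If they are too small, either program could be declared efficacious, or Online superior to Resources, more often than the protocol states.

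**Working it through.** **Inputs.** From the article: three visits; random intercept only; three pairwise models; Hochberg at 5%; 6-month change SD c = 5 kg; 36 men per group; 28% attrition; 150 men in total. Assumed, because the article does not give them: a = SD of 0-3 month change, b = SD of 3-6 month change.

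**The plan's own figure.** The article states: "Thirty six men in each treatment group will give the study 80% power to detect a difference in weight loss between groups of 4 kg". Its test is two-sided with alpha 0.015. The normal approximation is n = 2(2.432 + 0.842)² × 5²/4² = 33.5, so 34 per group. The exact t test gives 80.0% power at 35 and 81.3% at 36. Allowing for attrition, 108/0.72 = 150. The sizing reproduces. It uses the 6-month change SD directly, so this point does not touch it.

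**Standard error under the stated model.** With complete data the group-by-6-month coefficient is the difference in mean 0-6 month change, and the BMI term drops out of it. For three visits, the within-person variance is the sum of squared pairwise differences divided by 6, so the residual variance estimates (V03 + V36 + V06)/6. The model-implied variance of any change is twice that:

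implied Var(0-6 change) = (a² + b² + c²)/3, against the true c².

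SE ratio = √[(a² + b² + c²)/(3c²)].

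The ratio is below 1 exactly when a² + b² < 2c² = 50 kg². The approximate single-test error at nominal 5% is 2·P(Z > 1.96 × ratio).

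Example, a = 4, b = 3: (16 + 9 + 25)/75 = 0.667 and √0.667 = 0.816. At 36 per group the correct SE is 5 × √(2/36) = 1.18 kg and the model would report about 0.816 × 1.18 = 0.96 kg.

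**Range.** The correlation of successive changes is (c² − a² − b²)/(2ab). Family-wise error was simulated under the null with three arms, separate pairwise models and Hochberg.

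| a, b (kg) | a² + b² | Correlation of successive changes | SE ratio | Single-test error | Family-wise error |
|---|---|---|---|---|---|
| 6, 5 | 61 | −0.60 | 1.07 | 3.6% | about 3% |
| 5, 5 | 50 | −0.50 | 1.00 | 5.0% | about 5% |
| 4.5, 4.5 | 40.5 | −0.38 | 0.93 | 6.7% | about 7% |
| 5, 3 | 34 | −0.30 | 0.89 | 8.2% | about 9% |
| 4, 3 | 25 | 0 | 0.82 | 11% | about 13% |
| 3.5, 3 | 21.25 | +0.18 | 0.79 | 12% | about 15% |

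Independent increments with equal SDs (3.54, 3.54) also have a² + b² = 25 and give the same result as (4, 3). Because a + b cannot be less than c, the extreme is a = b = 2.5: ratio 0.71 and family-wise error about 22%. Using the 6-month change's own variance, the simulated family-wise error was between 4.2% and 4.7% in every setting.

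**With dropout.** REML random-intercept fits with 50 men per arm and 28% random dropout (1,500 trials per setting) agree:

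| a, b (kg) | True SD of estimate | Mean model SE | Rejection at nominal 5% |
|---|---|---|---|
| 3.54, 3.54 | 1.144 | 0.932 | 11.1% |
| 4, 3 | 1.121 | 0.939 | 10.1% |
| 4.5, 4.5 | 1.140 | 1.073 | 6.3% |
| 5, 5 | 1.155 | 1.154 | 5.4% |

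**The case against.** The strongest reply is that the result turns on two SDs that the article does not give. The rate is held at (5, 5) and the test is conservative at (6, 5). The (4, 3) and independent-increment cases are one condition, and (3.5, 3) needs early losers to go on losing more than others. The programs and their feedback end at 3 months. If the men who lost most then regain, successive changes are negatively correlated and the data move toward compound symmetry. This stands: neither the direction nor the size can be settled from the article.

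It does not remove the point, because protection needs strong reversal. With equal 3-month SDs the correlation of successive changes must be −0.5 or lower; at −0.38 family-wise error is already about 7%. Weight is measured in duplicate to within 0.1 kg, so measurement noise around a fixed personal weight is a poor description of changes with an SD of 5 kg. The pilot's sustained mean loss at 12 months gives no sign of general reversal, although a mean does not determine the correlation between individual changes.

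A second reply is that a condensed article may leave the residual structure to an analysis plan that is not shown. That plan could indeed add one. But the article expressly names the random intercept and claims the 5% rate, and the point is made against that statement.

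A third reply concerns the secondary outcomes. A reader might infer that they all carry standard errors that are too small. The article gives no variances for them, and where visit-to-visit noise dominates, as it may for blood pressure or step counts, change variance need not grow with the interval. No direction of error is claimed there.

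**Conclusion.** The point holds in conditional form. As written, the primary test has its stated 5% family-wise rate only if V03 + V36 ≥ 2 × V06, a condition that the article neither states nor supports. If the variance of weight change grows with time, which is plausible, the standard error of the 6-month contrast is 7% to 21% too small and family-wise error about 7% to 15% in the adverse scenarios tabulated. The mathematical limit is about 22%. These sizes rest on the protocol's 6-month SD of 5 kg, on assumed 3-month SDs, and on the ordinary reading of a random-intercept model with independent, constant-variance residuals.

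A reader might infer that the standard error is in fact too small and the 5% rate is in fact broken. The documents do not support that, because they give no 3-month SDs and some patterns leave the rate intact or make the test conservative. With complete data the 6-month estimate itself is unaffected, and so is the sample size calculation.

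**What to change.** For the primary outcome, replace the random-intercept-only structure with a repeated-measures linear model that has an unstructured 3×3 within-person covariance, fitted by REML. Alternatively, keep the random intercept and use participant-clustered robust standard errors. The fixed effects, the group-by-6-month contrast, the pairwise models and Hochberg's procedure can stay as they are. Use the same structure for the continuous secondary outcomes as a safeguard.

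The cost is one sentence of wording and one model option, with no new data. An unstructured covariance has six parameters against two for the random-intercept model. Standard errors may be larger: dividing 1 by the SE ratio gives increases of about 7% at (4.5, 4.5), 13% at (5, 3), 22% at (4, 3) and 27% at (3.5, 3). This loses nothing against the design, because the sample size was calculated from the 6-month change SD that the corrected analysis would use.

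### The BMI term in the planned weight model does not adjust the change that is tested, and baseline is subtracted with a fixed slope of 1: the analysis is valid but not fully efficient

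*Protocol article*

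**What the plan says.** Under Randomisation the article states: "Allocation was stratified by BMI category calculated at the baseline assessment (overweight, obese I, obese II". Under Statistical methods it fixes a mixed model with a random intercept per man, fitted separately for each pair of arms. The terms are group, time with three categorical levels (baseline, 3 months, 6 months) and group by time. Then: "The model will also include a term for the stratifying variable of BMI group at baseline". Efficacy is read from the coefficient for group at 6 months. No interaction of BMI group with time is named, although the section does spell out interactions with time for group and for the subgroup variables. Baseline is a response, and each group has its own free baseline mean. The same form carries over to the secondary outcomes: "Similar models will be used to examine differences in change in other outcome measures".

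The Sample size section rests on change: "The sample size calculation is based on the primary outcome of weight loss at 6 months". The SD of 5 kg given there is that of the change, not of weight itself.

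**The concern.** Allocation was stratified by BMI category, and the category was put in the model presumably so that the analysis reflects the stratification. A time-constant term cannot do that for a coefficient that measures change within a man, because it adds the same amount to his baseline, 3-month and 6-month values.

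Leaving the group means free at baseline has a related effect. Randomisation makes these means equal in expectation, but the model does not use that fact. Any chance baseline difference is subtracted in full instead of in proportion to how well baseline predicts follow-up. Precision is at stake, slightly for weight and possibly more for secondary outcomes that correlate less strongly over time. Hypotheses 1(b) and 2 of the article depend on those outcomes.

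**Working it through.** **1. The plan's own figures.** Inputs from Sample size: difference 4 kg, SD of weight loss 5 kg, two-sided alpha 0.015, power 80%, attrition 28%.
- Normal formula: n = 2 × (2.432 + 0.842)² × 5² / 4² = 33.5, so 34 per group.
- Noncentral t: power is 0.79986 at 35 per group and 0.813 at 36, so 36 is the smallest n that reaches 80%.
- Attrition: 3 × 36 = 108, and 108 / 0.72 = 150.

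Both stated figures reproduce. The SD is that of a change, which is the quantity the planned coefficient estimates.

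**2. What the BMI main effect does.** Write a man's expected weight at time t as group, time and group-by-time terms plus b(stratum). Then E(6 months) − E(baseline) contains b − b = 0. With complete data the group-by-6-month coefficient is therefore the difference in mean change, with or without b.

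This was checked on 150 simulated two-arm data sets with 50 men per arm, three BMI strata and a true difference of −4 kg:
- *Complete data.* The largest gap between the planned coefficient and the raw change difference was 8e-14 kg. The largest gap with versus without the BMI term was 1e-13 kg, and the largest gap in standard error was under 0.0001 kg.
- *28% missing at 6 months.* The identity no longer holds exactly. The BMI term moved single estimates by up to 0.21 kg, but the mean estimate only from −4.067 to −4.065. The planned coefficient differed from the completers' raw change difference by up to 0.53 kg.
- *Bias.* The planned model, the model with BMI by time, the raw change and baseline-adjusted regression all centred between −4.04 and −4.09.

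The simulation tests the identity and bias, not the gain. It generates change independently of baseline within stratum, and stratum explains only about 2% of the 6-month change variance: 0.56 / (0.56 + 24.49).

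**3. Fixed versus estimated slope on baseline, for weight.** With equal SD s at baseline and 6 months and correlation r, var(change) = 2s²(1 − r) and the baseline-adjusted variance is s²(1 − r²). The ratio is (1 + r)/2. The article does not give s, so 10 to 18 kg is assumed. A change SD of 5 kg then gives r = 1 − 25/(2s²).

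| s (kg) | r | variance ratio | effective SD (kg) | power at 36 |
|---|---|---|---|---|
| 10 | 0.875 | 0.938 | 4.84 | 0.841 |
| 14 | 0.936 | 0.968 | 4.92 | 0.827 |
| 18 | 0.961 | 0.981 | 4.95 | 0.822 |

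The planned analysis has power 0.813, so the gain is 0.9 to 2.8 points.

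**4. Letting stratum act on change.** Assume stratum shares of 0.4/0.4/0.2 and mean changes of −2.5/−4/−5.5 kg. The between-stratum variance is 1.26, or 1.26/25 = 5.0% of the change variance. Power at 36 would be 0.835. At 0% it stays at 0.813. This gain should not be added to that in step 3, because BMI stratum and baseline weight overlap.

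**5. Secondary outcomes.** With r = 0.5 to 0.7 (assumption) the ratio is (1 + 0.5)/2 = 0.75 to (1 + 0.7)/2 = 0.85. This is worth 1/0.85 − 1 = 18% to 1/0.75 − 1 = 33% more men.

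**6. Chance imbalance.** A baseline difference of d shifts the change-score estimate by −(1 − r)d relative to the adjusted one. For weight this is 0.04 to 0.13 kg per kg of imbalance.

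**The case against.** The strongest reply is that nothing here is wrong. The coefficient estimates the quantity the trial was sized on, the sizing reproduces, and the estimate is unbiased under randomisation. If stratum does predict change, leaving it out makes the test slightly conservative. The article also reports 159 men recruited against 150 required. All of this stands.

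The article says only that a term is included, and a fuller plan might specify BMI by time. That is possible. A main effect is still the natural reading, because the same section names interactions with time where it means them.

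The gains also rest on assumptions. Step 3 needs similar SDs at baseline and 6 months; if the true slope on baseline is 1, there is no gain. BMI by time costs four parameters (two stratum contrasts at two follow-up times) and pays only if stratum predicts change. In the simulation with missing data, adding it to the planned model did not reduce the spread of the estimates (SD 1.235 against 1.195 kg).

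A reader might infer that the planned analysis ignores the baseline value or the stratification altogether, or that chance imbalance biases the result. The article does not support this. Each man's baseline is subtracted, allocation itself was stratified, the BMI term does enter once data are incomplete, and the effect of imbalance on weight is small against a 4 kg target.

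**Conclusion.** This is a matter of efficiency, not an error in the primary analysis. Read as a main effect, the BMI term has no effect on the tested coefficient when data are complete and a trivial average effect at 28% missing. For weight, the precision left unused by fixing the baseline slope at 1 is worth about 1 to 3 power points at 36 per group. That rests on an assumed weight SD of 10 to 18 kg, equal at both times. The possible gain for secondary outcomes is larger, a variance factor of 0.75 to 0.85, but depends wholly on an assumed correlation of 0.5 to 0.7. No stated figure needs correction.

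**What to change.** Keep the repeated-measures model, but give the groups in each comparison a common baseline mean: time, and group by time at 3 and 6 months only. Replace the single BMI term with BMI stratum and BMI stratum by time. Read efficacy from the 6-month group contrast. Use the same form for each secondary outcome, with that outcome's own baseline as the first response. If the full plan already contains BMI by time, the article's sentence need only say so.

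This is preferable to modelling the 3- and 6-month values with baseline as a covariate. That version drops men with no follow-up, whereas the Abstract promises an intention-to-treat analysis of all randomised men.

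The cost is a change of wording and four extra parameters per model. Every variable is already collected and the sample size is unaffected. The change should be fixed and dated before the follow-up outcomes are analysed by group.

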### The SHED-IT pilot study

In 2007/2008, we conducted the first randomised controlled trial of an online weight loss program that targeted men exclusively [23-26]. Sixty-five overweight/obese male staff and students of the University of Newcastle were recruited and randomly assigned to either an (i) Internet group or (ii) Information only group. Both groups received one face-to-face information session and a program booklet. Internet group participants were instructed to use the study website for three months. 'Intention-to-treat' analysis revealed significant and sustained weight loss of -5.3 kg at 12 months for the Internet group and -3.1 kg for the Information only group with no significant group difference [26].

Both the Internet and Information only programs were effective, but those participants who complied with the recommended Internet features were able to maintain significantly greater weight loss than those who did not comply [24,26]. A key feature of both programs was the low level of interaction between the researchers and participants, which highlighted the potential of SHED-IT as a cost effective approach to weight loss for men at a population level. The Information only group was an effective low dose treatment option, but we were unable to establish if it was the face-to-face information session, or the provided resources that were most effective.

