#### (i) SHED-IT Resources

Participants randomised to this group were provided with a weight loss resource package, which included:

- a 25-minute SHED-IT DVD presentation on weight loss for men;

- the SHED-IT *Weight Loss Handbook for Blokes (NB: 'Blokes' is Australian vernacular meaning men)*;

- the SHED-IT *Weight Loss Support Book for Blokes;*

- a pedometer, tape measure for waist circumference measurement and a kilojoule (kJ) counter book.

The SHED-IT resources have been tailored for men, based on our pilot process evaluation [26] and include examples and scenarios that men can relate to and commonly experience. Both the DVD and *SHED-IT Weight Loss Handbook for Blokes *include basic weight loss information (energy balance, calculating total energy expenditure and tracking energy intake) and outline nine key weight loss messages tailored for men. Through the handbook, men are instructed: to measure and record their weight (in kg) and their waist circumference (in cm) once each week; to complete daily eating and exercise diaries for four days each week (including 2 weekdays and 2 weekend days); to record their step counts for four days each week (including 2 weekdays and 2 weekend days); and to identify and record sources of social support; and personal weight, physical activity and eating goals each month for 3 months. The *SHED-IT Weight Loss Support Book for Blokes *contains instructions for calculating both resting metabolic rate and total kJ expenditure; how to plot weight loss, waist circumference loss and weekly average step charts for recording and monitoring progress; space for recording body weight, physical activity and eating goals; space for recording social support strategies; and a daily food and exercise diary to complete.

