#### (ii) SHED-IT Online

In addition to receiving all of the materials from the SHED-IT *Resources *intervention, participants randomised to the SHED-IT *Online *group have access to the freely available commercial *Calorie King*™ (Australia) website (http://www.calorieking.com.au) and a website user guide. *Calorie King*™ is an online, behaviour therapy health website that provides tools and information to help individuals improve their diet and physical activity levels. The *SHED-IT Weight Loss Handbook for Blokes *and the *SHED-IT Weight Loss Support Book for Blokes *were modified slightly with instructions to use the online 'Healthy Lifestyle Diary' for four days each week (including 2 weekdays and 2 weekend days) in place of the paper-based food and exercise diary. Participants were asked to 'weigh-in' on the website at least once a week. As in the SHED-IT *Resources *intervention, men were advised to use their *Weight Loss Support Book for Blokes *to document all other key self-monitoring behaviours, social support strategies and individual goals.

Over the course of the three months, each participant will be emailed seven individualised feedback sheets. Diaries will be reviewed weekly in the 1^st ^month, fortnightly in the 2^nd ^month and once in the 3^rd ^month. This feedback will be provided by research assistants using a standardised set of feedback sheets and will target strategies to address weight loss, reduce energy intake and increase energy expenditure. The feedback is designed to provide general encouragement and specific strategies to address those aspects of the diary entries that are furthest from ideal and/or require the greatest degree of improvement. Participants will be able to record and self-monitor their weight change, energy intake and daily exercise online. These activities are recognised as cornerstones of behavioural treatment [32]. Participants who have not checked-in for 2 weeks will be reminded via email and SMS. Participants are also able to email any questions through to the study email address.

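### The analysis labelled per protocol compares adherent with non-adherent men inside each arm, so it is a self-selected adherence association and not an estimate of programme effect

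*Protocol article*

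**What the plan says.** The last paragraph of Statistical methods introduces the analysis: "A per protocol analysis will also be conducted and include men who complied with treatment from the" two intervention arms, Online and Resources. Good compliance is defined as "completion of requested daily eating and exercise diaries (n >40) over the 3-month period and weekly check-ins (n >10"). The comparison then stated is: "Results of the per-protocol group will be compared with non-compliers in each group i.e. those who did not meet the above adherence recommendations". No comparison of adherent men with Control is given, and no caution on interpretation is attached.

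The check-in criterion appears to be a count of weigh-ins. Process measures states: "Adherence to self-monitoring (total number of daily diet entries, daily exercise entries and weekly weigh-ins) will be calculated from diaries for both treatment arms". The Online intervention section says: "Participants were asked to 'weigh-in' on the website at least once a week". The primary outcome is body weight.

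Elsewhere in Statistical methods, efficacy is decided by the group-by-6-month interaction between randomised arms, with Hochberg control over the three pairwise comparisons. All secondary hypothesis tests are set at a two-sided 5% level.

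**The concern.** A per-protocol analysis normally asks what the treatment does, against the randomised comparator, when taken as planned. Here the comparator is the less adherent men of the same arm. Both groups were assigned the same programme, and what separates them is their own behaviour after randomisation. Randomisation therefore gives no protection against differences in motivation, health, time or support that affect both diary-keeping and weight.

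The weigh-in criterion adds a second route. A man who is losing weight has reason to keep stepping on the scale, and the 3-month adherence window runs up to the 3-month weight measurement. Part of any association could run from outcome to adherence.

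What is at stake is interpretation. The article reports from the pilot that "those participants who complied with the recommended Internet features were able to maintain significantly greater weight loss than those who did not comply", although the randomised pilot groups did not differ significantly. The new trial repeats that type of contrast under a label that suggests efficacy.

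**Working it through.** **Inputs from the protocol article**
- SD of 6-month weight loss: 5 kg (Sample size).
- Men per arm: 36 evaluable (Sample size), or 159/3 = 53 recruited (Abstract).
- Adherence rule: more than 40 diaries and more than 10 check-ins over 3 months (Statistical methods).
- Diary request: "to complete daily eating and exercise diaries for four days each week (including 2 weekdays and 2 weekend days"), for 3 months.

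**Inputs assumed, because the documents do not give them**
- Share of men adherent, p: 20% to 50%.
- Correlation between the tendency to adhere and weight loss, rho: 0 to 0.5.

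**1. The plan's own figure.** No figure is stated for this comparison. The sample size that supplies the SD does reproduce. For 4 kg, SD 5 kg and two-sided alpha 0.015, a two-sample t-test has 79.99% power with 35 men per group and 81.3% with 36. Allowing for 28% attrition, 36/0.72 = 50 per group, or 150 in total. That calculation is not in dispute.

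**2. How strict the rule is.** Four days a week for 12 to 13 weeks is 48 to 52 diaries. At least 41 are needed, which is 41/52 = 79% to 41/48 = 85%. At least 11 check-ins out of 12 to 13 are needed, which is 11/13 = 85% to 11/12 = 92%. A man can use most of the programme and still be classed as a non-complier.

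**3. Expected gap with no programme effect.** Let adherence be a latent normal variable correlated rho with the man's own weight loss, and let the top fraction p be classed as adherent. Then

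gap = rho × SD × phi(z_p) / (p(1 − p)),

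where z_p is the normal cut-off and phi the normal density.

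- p = 0.4: phi = 0.386 and p(1 − p) = 0.24, so gap = rho × 5 × 1.61 = 8.05 × rho.
- p = 0.2: phi = 0.280 and p(1 − p) = 0.16, so gap = rho × 5 × 1.75 = 8.75 × rho.

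| rho | p = 0.4 | p = 0.2 |
|---|---|---|
| 0 | 0 kg | 0 kg |
| 0.2 | 1.61 kg | 1.75 kg |
| 0.3 | 2.41 kg | 2.62 kg |
| 0.4 | 3.22 kg | 3.50 kg |

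At rho = 0.5 and p of 20% to 50%, the gap is 4.0 to 4.4 kg, about the trial's own 4 kg target difference.

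**4. Chance of a significant result favouring adherent men.** This was simulated within one arm with zero programme effect, a two-sided 5% t-test, 20,000 trials per setting and p of 20% to 50%.

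| rho | 36 men | 53 men |
|---|---|---|
| 0 | about 2.5% | about 2.5% |
| 0.2 | 13–15% | 16–21% |
| 0.3 | 24–29% | 33–42% |
| 0.5 | 57–71% | 75–87% |

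**The case against.** The strongest reply is that nothing decisive rests on this analysis. Efficacy is judged on the between-arm 6-month term, the Abstract commits to intention-to-treat with all randomised men, and the adherence comparison is an addition. That stands, and it limits the point to how one supplementary result is labelled, tested and read.

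It is also fair that rho and the share adherent appear nowhere in the documents. A reader might infer that the contrast is bound to show a benefit even if the programmes do nothing. The documents do not support that: at rho = 0 there is no bias, and at rho = 0.2 a significant result remains uncommon. Reverse causation through weigh-ins is likewise plausible but not shown. Weigh-ins are one of two joint criteria, and the primary endpoint falls three months after the adherence window closes.

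Two further inferences should be resisted. A reader might suppose that Resources men who do not hand in their booklet are counted as non-compliers, but no rule for unreturned booklets is given, and an article may leave that to the full protocol. A reader might also object that adherent men differ between arms, but the stated comparison is within each arm and no cross-arm comparison of adherent men is planned.

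Finally, the wording does not forbid a further comparison of adherent men with Control. None is stated, however, and a direct one would be self-selected too.

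**Conclusion.** The point holds in limited form. As written, the analysis is not a per-protocol estimate of programme effect: it omits Control and compares groups formed by the men's own behaviour after randomisation, partly through an act tied to the primary outcome. If adherence and weight loss share causes, it would be expected to favour adherent men under a null programme effect, by about 1.6 to 3.5 kg for rho of 0.2 to 0.4 and 20% to 40% adherent. That size rests on the protocol's SD of 5 kg, a latent-normal model, and assumed values of rho and p. The direction rests on a positive correlation. The primary intention-to-treat conclusion is unaffected. What changes is what the trial may claim from its adherence data.

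**What to change.** In the last paragraph of Statistical methods:
- Drop the per-protocol label and call the comparison a descriptive, non-randomised adherence association within each arm.
- Report estimates with confidence intervals, with no efficacy test and no efficacy wording. Exclude it from the secondary hypothesis tests run at 5%.
- State that programme efficacy rests only on the randomised between-arm comparisons.

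This costs a few sentences and needs no new data.

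A complier-average causal effect against Control, using randomised group as the instrument, may be added as an optional sensitivity analysis. It divides the intention-to-treat difference by the share adherent, and so assumes that assignment had no effect in non-compliers. That is doubtful here, because men who fall just short of the diary threshold still received the DVD, handbook and pedometer. The consequence can be large: a 4 kg intention-to-treat difference would become 4/0.4 = 10 kg at 40% adherent and 4/0.2 = 20 kg at 20%. If it is reported, the assumption and its weakness should be stated beside the estimate. Its cost is some extra analysis and wider intervals.
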